## Participants and methods

### Participants

Study participants have been selected from the Metabolic Syndrome in Men (METSIM) study, which includes 10,197 men, aged from 45 to 73 years at baseline, randomly selected from the population register of the Kuopio town (baseline examination in 2005–2010) (10). The aim of the METSIM study is to investigate genetic and non-genetic factors associated with the risk of T2D, CVD, and insulin resistance-related traits.

The *inclusion criteria* for the present study were 1) IFG at entry (fasting plasma glucose 5.6–6.9 mmol/l) and with (2-h glucose 7.8–11.0 mmol/l) or without IGT (2-h glucose <7.8 mmol/l), and HbA1c <48 mmol/mol (<6.5%), 2) age 50–75 years, 3) body mass index (BMI) ≥25 kg/m^2^, and 4) the genetic risk score (GRS) (low risk 1–2 quintiles of the GRS and high risk 4–5 quintiles of the GRS). The *exclusion criteria* were 1) age <50 years or >75 years, 2) BMI <25 kg/m^2^, 3) type 1 or type 2 diabetes or isolated IGT (2-h plasma glucose <5.6 mmol/l and 2-h plasma glucose 7.8–11.0 mmol/l) or HbA1c ≥48 mmol/mol (≥6.5%), and 4) chronic diseases preventing to participate in the trial. After the identification of potential participants of the METSIM study, they were approached by an invitation letter.

The GRS in the present study was calculated on the basis of the number of risk alleles of 76 genetic variants increasing the risk for T2D as previously published (11). During the planning phase of the present study, less than 100 genetic variants increasing the risk for T2D had been published. A total of 600 participants were recruited and divided into two intervention groups (Fig. 1). Study participants, laboratory personnel, and clinical nutritionists were blinded with respect to the GRS of the participants throughout the study.

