**Methods:**

Both intervention and control groups include 300 participants with low and 300 participants with high genetic risk for T2D. Genetic risk was evaluated by genetic risk score, and these two groups were matched additionally for fasting plasma glucose concentration, age, and body mass index. Corresponding control groups (300 participants each) do not have lifestyle intervention. The inclusion criteria are impaired fasting glucose at entry with or without impaired glucose tolerance, age 50–75 years, and body mass index ≥25 kg/m^2^. The primary outcome is incident T2D and the intervention lasts for 3 years.

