**Fig. 1 F0001:**
[figure not shown]
Study design of the T2D-GENE trial. Participants in the intervention and control groups of the trial are divided into two groups based on the genetic risk score for type 2 diabetes (low genetic risk and high genetic risk). IFG, impaired fasting glucose; IGT, impaired glucose tolerance. The duration of the intervention is follow-up time is 3 years for all participants.

For both intervention groups (low GRS and high GRS), control groups of 300 participants (altogether 600 participants) of the METSIM study were selected and matched for GRS, fasting plasma glucose concentration, age, and BMI (Fig. 1). The rationale for these two control groups is to compare the incidence of T2D during the intervention between the two intervention groups and the two control groups.

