### Statistical analyses

The primary analyses for the outcomes (incident T2D) in the time-to-event analyses will be based on a Cox proportional-hazards model with the study group (intervention and control) as a covariate in the low and high GRS groups. Linear regression will be used to evaluate the effect of intervention on insulin sensitivity, insulin secretion, the glucose AUC, and other continuous variables. Comparison between the study groups at baseline and at the end of 3-year intervention will be carried out with t-test (continuous variables) intervention and chi-square test (non-continuous variables).

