### Time table

The first participants started the intervention in April 2016, and the recruitment was completed in April 2018. Altogether 635 participants were recruited. The first participants finished the 3-year intervention in April 2019, and the last participants will finish it in September 2021. The last participants in the control group will have a 3-year visit in September 2021.

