### Baseline data

The baseline characteristics of the participants in the intervention groups are presented in Table 2 (low and high genetic risk groups combined). The mean age of the participants was 65.0±5.9 years (mean ± SD) at the baseline, and they were obese with the mean waist circumference higher than recommended. Fasting plasma glucose concentration was within the range of IFG (5.6–6.9 mmol/l), 2-h glucose concentration <11.1 mmol/l, and HbA1c (<48 mmol/l or <6.5 %). Blood pressure and concentrations of total and LDL cholesterol were slightly higher than recommended.

**Table 2 T0002:** Baseline characteristics of the participants in the intervention group (*n* = 635)

Variables	Range	Mean ± SD
Age, years	51–75	65.0±5.9
Body mass index, kg/m^2^	25.0–48.5	28.7±3.2
Waist circumference, cm	84.0–149.0	103.3±9.0
Systolic blood pressure, mmHg	101–193	134±15
Diastolic blood pressure, mmHg	60–117	84±9
Fasting glucose, mmol/l	5.6–6.9	6.0±0.3
2-h glucose, mmol/l	2.7–10.9	6.3±1.6
HbA1c, mmol/mol	29–45	37.5±3.1
Total cholesterol, mmol/l	2.49–7.91	5.03±1.00
Low density lipoprotein-cholesterol, mmol/l	1.05–5.88	3.10±0.90
high density lipoprotein-cholesterol, mmol/l	0.60–2.80	1.38±0.36
Total triglycerides, mmol/l	0.46–5.73	1.37±0.67

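### The article gives the intervention group as both 600 and 635 without a split by genetic risk, and compares it with 600 selected controls in a Cox model whose only named covariate is study group

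*Protocol article*

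**What the plan says.** All places are in the Protocol article.

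- **Abstract, Methods:** "Both intervention and control groups include 300 participants with low and 300 participants with high genetic risk for T2D".
- **Participants:** "A total of 600 participants were recruited and divided into two intervention groups".
- **Participants, text after Fig. 1:** "control groups of 300 participants (altogether 600 participants) of the METSIM study were selected and matched for GRS"; the other matching variables are fasting glucose, age and BMI.
- **Time table:** "Altogether 635 participants were recruited".
- **Baseline data:** Table 2 is titled "Baseline characteristics of the participants in the intervention group", with n = 635 and both GRS groups combined.
- **Statistical analyses:** the primary model for incident diabetes is a "Cox proportional-hazards model with the study group (intervention and control) as a covariate in the low and high GRS groups". No other covariate and no pair stratum is named.

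**The concern.** Two different numbers are reported as recruited to the same arm. Both are in the past tense, so they do not read as a target and an achieved figure. The contrast between GRS groups is the purpose of the trial, yet a reader cannot tell how many men are in each intervention GRS group, or whether the excess over 300 is shared evenly.

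The article describes no randomisation. Controls were selected from the parent cohort, so comparability with the intervention men rests on the matching. If the controls were chosen to resemble groups of 300 and the intervention groups are larger, the balance achieved on the matching variables is not known from the text. The primary model, as stated, does not adjust for what remains.

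**Working it through.** **1. The counts.**

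| Source | Intervention | Control |
|---|---|---|
| Abstract | 300 + 300 = 600 | 300 + 300 = 600 |
| Participants | 600 | 300 + 300 = 600 |
| Time table | 635 | not given |
| Table 2 | 635, GRS groups combined | not given |

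635 − 600 = 35, and 35/635 = 5.5%. Table 2 is labelled as the intervention group, so the 635 cannot include controls.

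**2. Possible explanations within the text.**

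- *Ineligible men.* The Table 2 ranges (age 51–75, BMI 25.0–48.5, fasting glucose 5.6–6.9, HbA1c 29–45) all lie inside the inclusion limits. The accompanying text says the table combines the low and high genetic risk groups. The table therefore gives no sign that 35 of the 635 were ineligible.
- *Dropout allowance.* The sample size section raises 267 for about 10% dropout: 267/0.9 = 297, about 300 per group. That step reproduces, and the allowance is already inside the 300. The extra 35 lie beyond it, and no reason is given.

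**3. The split by GRS.** An even split is about 318 and 317. If each group reached at least 300 (an assumption), the split lies between 335/300 and 300/335.

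**4. Whether the stated analysis can take all 635.** The matching is described for groups, with no pairs and no 1:1 ratio. The Cox model has study group as a covariate within each GRS group. Unequal arms are admissible.

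**5. Effect on power of keeping all 635.** Inputs: control risk 23% and a 6-point effect (so 17%), both from the sample size section; two-sided α = 0.05 (sidedness is not stated, so assumed); 300 controls per GRS group; 635/2 = 317.5 intervention men per GRS group (even split assumed).

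Power = Φ{[|p1 − p2| − 1.96·√(p̄(1 − p̄)(1/n1 + 1/n2))] / √(p1(1 − p1)/n1 + p2(1 − p2)/n2)}, where p̄ is the pooled risk.

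- 300 v 300: p̄ = 0.200; (0.06 − 1.96 × 0.03266)/0.03257 = −0.123; power 45.1%.
- 300 v 317.5: p̄ = 0.199; (0.06 − 1.96 × 0.03216)/0.03217 = −0.094; power 46.3%.
- For 23% v 10%, the same formula gives 99.1% and 99.2%.

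The extra men change power by about 1 point or less. The 45.1% is far from the 95% that the article states; that is a separate matter and does not bear on this point.

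**The case against.** The strongest defence is that 300 + 300 is the planned size and 635 the achieved recruitment. The larger figure is reported openly in two places, and rules for analysis sets and covariates commonly sit in a full protocol or SAP that is not shown. Much of this stands. The absence of an analysis-set definition from a condensed article is no fault. It does not rescue the Participants section, which reports 600 as recruited, nor supply the GRS split.

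A reader might infer something stronger: that 35 intervention men have no counterpart in the comparison, and that the group could be cut to 600 after outcomes are known, since the first participants finished in April 2019 and the last were due in September 2021. The documents do not support this. Group matching gives no man an individual counterpart to lack, the model needs no equal arms, and no sentence says that anyone will be left out.

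The size of such a removal would also be pure assumption. Take the 17% risk of the 6-point scenario and suppose that the 35 removed had a 20% risk (7 cases; the 20% is not in the documents). Then (635 × 0.17 − 7)/600 = 16.8%, a shift of about 0.2 points. If all 35 came from one GRS group, (335 × 0.17 − 7)/300 = 16.65%, about 0.35 points. The limits for the whole group are (107.95 − 35)/600 = 12.2% if all 35 were cases and 107.95/600 = 18.0% if none were. These figures describe a step that nobody has planned.

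**Conclusion.** The point holds as a minor one. The Participants section and the abstract give an intervention group of 600, while the Time table and Table 2 give 635, a difference of 35 men (5.5%). The split by GRS is missing from the article. I take 635 as the actual figure because it carries the baseline data.

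No bias is demonstrated, and the effect on power is negligible under an even split. What remains is a wrong recruited number, and a comparison of 635 intervention men with 600 group-matched, non-randomised controls through a model that names only study group. Adjusting for the matching variables would improve that model whichever way the extra 35 men are divided.

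**What to change.** 1. Correct the abstract and the Participants section to the 635 actually recruited, and give that number by GRS group.
2. State that all 635 intervention men and all selected controls enter the primary analysis.
3. In the Statistical analyses section, add fasting glucose, age and BMI as covariates in the Cox model. Add GRS as well, since each stratum spans two quintiles and the score still varies within it. Unequal numbers or residual imbalance on these variables are then less able to distort the comparison.

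Cost: a few sentences and slightly more analysis work. The matching variables are already collected, so no new participants or visits are needed.

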**Fig. 1 F0001:**
[figure not shown]
Study design of the T2D-GENE trial. Participants in the intervention and control groups of the trial are divided into two groups based on the genetic risk score for type 2 diabetes (low genetic risk and high genetic risk). IFG, impaired fasting glucose; IGT, impaired glucose tolerance. The duration of the intervention is follow-up time is 3 years for all participants.

For both intervention groups (low GRS and high GRS), control groups of 300 participants (altogether 600 participants) of the METSIM study were selected and matched for GRS, fasting plasma glucose concentration, age, and BMI (Fig. 1). The rationale for these two control groups is to compare the incidence of T2D during the intervention between the two intervention groups and the two control groups.

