Several diabetes prevention trials have been published on the effects of lifestyle changes (diet and physical activity), and a meta-analysis of these trials reported a 57% reduction in incident T2D (8). There are no previous trials investigating the effect of the genetic background of the participants (the number of the risk alleles for T2D) on the effect of the prevention of T2D. Therefore, the aim of the T2D-GENE trial is to investigate the effects of lifestyle intervention (diet, physical activity, and weight maintenance/weight loss) on the prevention of incident T2D and the worsening of hyperglycemia in people with a high number of T2D risk alleles compared with people with a low number of T2D risk alleles. The second aim of our study is to investigate whether a group-based intervention utilizing a website is as effective as is an individual-based intervention. The hypotheses of the study are that lifestyle intervention is efficient independent of the number of T2D risk alleles (high and low genetic risks of T2D), and that a group-based intervention is as effective as an individual-based intervention in the prevention of T2D.

The primary outcome of our study is incident T2D defined by fasting plasma glucose ≥7.0 mmol/l or 2-h glucose ≥11.1 mmol/l in an oral glucose tolerance test (OGTT) or HbA1c ≥ 47 mmol/mol (6.5%), according to the American Diabetes Association criteria (9), or drug treatment for T2D started during a 3-year intervention trial. The secondary outcomes are changes in glucose area under the curve (AUC) in an OGTT, changes in insulin secretion and insulin sensitivity, and incident cardiovascular disease (CVD) events (fatal or non-fatal myocardial infarction, fatal or non-fatal stroke, death from cardiovascular causes or incident heart failure).

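### The primary Cox model does not suit an outcome that is tested once after baseline in controls: if T2D is dated at the visit, small arm differences in visit timing can move the hazard ratio across 1

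*Protocol article*

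**What the plan says.** All references are to the protocol article.

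- **Model.** Under Statistical analyses, the primary "time-to-event analyses will be based on a Cox proportional-hazards model", comparing intervention with control within the low and the high GRS group.
- **Outcome.** The introduction defines incident T2D by fasting glucose, 2-hour glucose or HbA1c thresholds, or by "drug treatment for T2D started during a 3-year intervention trial".
- **Testing.** Under Study visits, the intervention groups have laboratory visits at 0, 1, 2 and 3 years. The 1-year visit has a non-fasting HbA1c only. Controls have laboratory visits at 0 and 3 years.
- **Duration.** The Fig. 1 legend: "The duration of the intervention is follow-up time is 3 years for all participants".
- **Calendar.** Under Time table: "The first participants started the intervention in April 2016, and the recruitment was completed in April 2018". Then: "The first participants finished the 3-year intervention in April 2019, and the last participants will finish it in September 2021". For controls it gives one date: "The last participants in the control group will have a 3-year visit in September 2021".
- **Controls.** They were selected from the parent cohort and matched on GRS, fasting glucose, age and BMI. No random allocation is described, and no start dates are given for them.

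**The concern.** A Cox model compares people only within the set still at risk at each event time. It therefore needs event times that reflect when the disease arose. For T2D found at a laboratory visit, the plan's data give only an interval: after the last negative test and no later than the visit. In controls that interval is the whole 3 years.

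If the visit date is used as an exact event time, most events fall in a narrow band around month 36, and their order within that band is the order of appointments. A man whose final visit is two weeks later counts as event-free for every event dated before it, whether or not he already has diabetes. When one arm is on average seen slightly later, its events are pushed behind those of the other arm, and the hazard ratio shifts for reasons of scheduling.

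What is at stake is the primary comparison in each GRS group, and with it the comparison of effect between GRS groups. The controls were matched and no random allocation is described, so the design does not by itself make visit timing comparable between arms.

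**Working it through.** **1. Dates.** First participants: April 2016 to April 2019 = 36 months. Last participants: April 2018 (end of recruitment) to September 2021 = 41 months, which is 5 more than 36. A September 2021 finish after exactly 3 years implies a start in September 2018, 5 months after recruitment closed.

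**2. Inputs for the hazard ratio.** The sample-size section gives 23% T2D at 3 years in controls and a reduced effect of 6 points, hence 17% with intervention. With constant hazards:

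- control: −ln(1 − 0.23)/3 = 0.0871 per year
- intervention: −ln(1 − 0.17)/3 = 0.0621 per year
- true hazard ratio: 0.0621/0.0871 = 0.71

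**3. Effect of late visits on event counts.** At 41 months the risks are 1 − exp(−0.0871 × 41/12) = 25.7% and 1 − exp(−0.0621 × 41/12) = 19.1%. Even 5 extra months for everyone add only 2.7 and 2.1 points. Extra events are therefore not the main problem.

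**4. Effect on a visit-dated Cox model.** Simulation with 300 per arm, exponential onset, tests at 12, 24 and 36 months (intervention) or 36 months only (control), Efron ties, median of 400 runs. Assumptions not in the article: the 1-year HbA1c finds half of prevalent T2D; the share of events dated by drug start is 0%, 30% or 50%; the visit-time differences are as listed.

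| Final visit timing | 0% drug-dated | 30% | 50% |
|---|---|---|---|
| Both arms exactly at 36 months | 0.76 | 0.75 | 0.74 |
| Both arms 0–5 months late, same distribution | 0.83 | 0.80 | 0.75 |
| Controls 1 month later on average (SD 1 month) | 1.67 | 1.32 | 1.10 |
| Intervention 1 month later on average (SD 1 month) | 0.47 | 0.52 | 0.56 |

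A further simulation with the same schedule, 30% drug-dated events and a half-month arm difference gives 1.12 (controls later) or 0.59 (intervention later). The tighter the visit dates cluster within each arm, the more a given difference moves the ratio, so these figures show the order of size and are not forecasts.

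The values of 0.74 to 0.83 under equal timing exceed 0.71 because the extra 1- and 2-year tests bring intervention events forward.

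**5. The limiting case.** If all controls were seen at month 41, all intervention men at month 36, and no event were dated by drug start, no intervention man would be at risk when any control event occurred. The Cox hazard ratio would then have no finite estimate, although the 3-year risks are still 23% and 17%.

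**6. Alternatives on the same risks.**

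- *Nominal (grouped) dating.* Even a full 5-month delay in one arm only rescales the ratio: 0.713 × 36/41 = 0.63 (controls late) or 0.713 × 41/36 = 0.81 (intervention late).
- *Complementary log-log with offset.* Under a constant hazard λ and m months of follow-up, P(T2D by m) = 1 − exp(−λ·m·e^{βx}), so log(−log(1 − P)) = log λ + log m + βx. Entering log m as an offset makes e^β the hazard ratio. In the half-month scenarios of step 4 this gave 0.71 to 0.72.

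**The case against.** **The 41 months need not be follow-up.** They run from the end of recruitment, while the Time table itself calls the period a 3-year intervention and the controls' last assessment a 3-year visit. The Intervention section offers a plausible reason for a start lag: the opening session takes about 150 men at a time. With 635 recruited over 24 months that is 635/150 = 4.2 batches, or one about every 24/4.2 = 5.7 months if intake was even. This stands. A reader might infer that some men were followed for 41 months, or that follow-up differed between men. The documents do not support that.

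**Unequal lateness between arms is hypothetical.** The only timing given by arm is that both finish in the same month, and equal lateness does little harm. This also stands: a reader should not infer that controls, or intervention men, were in fact seen later. A shared last month does not, however, show that the distributions of visit times agree.

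**Controls can become events before the last visit.** Drug starts count and can be dated. It would be too strong to say that T2D in controls is found only at the final visit. The table shows that drug-dated events reduce the sensitivity, but it remains material at 30% and 50%.

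**No dating rule is stated.** Visit windows and event dating are commonly left to the full protocol or SAP, so their absence here is no finding. If nominal dates are used, sensitivity to lateness is small. This makes the concern conditional. What the article does fix is a Cox model for an outcome whose glycaemic part is observed once in controls and more often in the intervention arm, and a better-suited model is available at almost no cost.

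**Conclusion.** The point holds as a conditional weakness of the stated primary model. It is not a demonstrated bias. If visit-detected T2D is entered at the visit date as an exact time, a half-month arm difference in final visits is enough to turn a true hazard ratio of 0.71 into about 1.1 or 0.6, and a one-month difference into 1.32 or 0.52, both with 30% of events dated by drug start. With equal timing it is about 0.8, and nominal dating removes most of the sensitivity to lateness.

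These sizes rest on constant hazards from the article's own 23% and 17%, and on assumed values for the drug-dated share, the 1-year test's detection rate, the spread of visit dates and the arm difference. None of the assumed values can be read from the article.

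The timetable shows only that the Fig. 1 legend and the Time table need to be reconciled. The case for change is that the alternative is more suitable and cheap.

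**What to change.** 1. In Statistical analyses, set time zero at the 0-year laboratory visit in both arms.
2. Replace the Cox model with the visit date as event time by an analysis that treats visit-detected T2D as interval-censored or grouped. Two options, each fitted within the GRS groups:
   - a complementary log-log model for T2D by the final visit, with log(months from the 0-year visit) as offset;
   - interval-censored proportional hazards, with each visit-detected case placed between the last negative test and the visit that found it, and drug starts entered at their own dates. This option also uses the 1- and 2-year tests.
3. Reconcile the Fig. 1 legend with the Time table: state whether the intervention began after recruitment and, if follow-up varied, give its actual range.
4. Report months from the 0-year to the final visit by arm and GRS group.

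Cost: a change of wording and a different model call, using visit dates that the trial should already hold. The downside is a model slightly less familiar to readers than Cox. The offset version also assumes a roughly constant hazard, which the interval-censored version can relax.

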## Methods

### Study visits

Participants in the intervention groups have four laboratory visits (0, 1, 2, and 3 years), and participants in the control groups have two laboratory visits (0 and 3 years) (Fig. 2). The study visits at 0 and 3 years include a questionnaire on physical activity at work and leisure time, smoking, alcohol use, history of diseases, and current medication, and dietary habits (food frequency questionnaire), blood pressure (three measurements 1 min apart), body weight, height, and bioimpedance for measure fat percentage. Laboratory measurements include an OGTT (plasma glucose and insulin concentrations at 0, 30, and 120 min), HbA1c, and concentrations of total LDL and HDL cholesterol, total triglycerides, alanine aminotransferase, creatinine, interleukin 1 receptor antagonist, and high sensitivity C-reactive protein. The three-factor eating questionnaire R18 (TFEQ-R18) (12) is used for the evaluation of participants’ eating behavior (cognitive restraint, uncontrolled eating, and emotional eating) during the intervention. In the intervention group, the 1-year visit includes measurement of non-fasting HbA1c. At the 2-year visit, the TFEQ-R18 questionnaire is filled, and body weight, blood pressure, and the laboratory measurements are performed similarly as at 0-year and 3-year visits.

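### Controls are matched, not randomised, and the stated primary Cox model names no adjustment for baseline 2-h glucose or HbA1c, two of the measurements that define the outcome

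*Protocol article*

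**What the plan says.** **How the groups were formed.** Under Participants, eligible men in the METSIM cohort were identified and then "they were approached by an invitation letter". The next step is "A total of 600 participants were recruited and divided into two intervention groups"; this division is by genetic risk score (GRS), not between intervention and control. The 600 controls are described after Fig. 1: they "of the METSIM study were selected and matched for GRS, fasting plasma glucose concentration, age, and BMI". The abstract (Methods) says "these two groups were matched additionally for fasting plasma glucose concentration, age, and body mass index". That sentence can be read as matching the low-GRS and high-GRS groups to each other, but on either reading 2-h glucose and HbA1c are not listed.

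**What counts as an event.** The introduction defines incident type 2 diabetes by "fasting plasma glucose ≥7.0 mmol/l or 2-h glucose ≥11.1 mmol/l in an oral glucose tolerance test (OGTT) or HbA1c ≥ 47 mmol/mol (6.5"%), or by the start of drug treatment for diabetes.

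**The primary model.** Statistical analyses gives a "Cox proportional-hazards model with the study group (intervention and control) as a covariate in the low and high GRS groups". It names no further covariate and no handling of the matching.

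**What is measured at baseline.** Study visits has controls attending at years 0 and 3. Visits at those times include the OGTT, HbA1c and a food frequency questionnaire. In addition, "The study visits at 0 and 3 years include a questionnaire on physical activity at work and leisure time, smoking, alcohol use".

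**The concern.** A Cox model with treatment group alone is defensible under randomisation, because baseline differences then arise only by chance and the test allows for them. Here, confounding is controlled only by the eligibility limits and four matching factors. Of the three glycaemic measurements that can trigger the outcome, only fasting glucose is matched.

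Eligibility admits men with and without impaired glucose tolerance. Some therefore start close to the 2-h threshold of 11.1 mmol/l and others far below it, and nothing in the stated plan equalises that mix between the groups. If the mix differs, the difference enters the hazard ratio in each GRS group and would be reported as an effect of the intervention, or would hide a real one. A larger sample does not remove this error.

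**Working it through.** **1. Is there random allocation?** The article uses random selection only for the METSIM population sample (Participants), and randomisation only for earlier prevention trials (introduction). The intervention men were invited and split by GRS; the controls were selected to match. The comparison is a matched, non-randomised one.

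**2. Which outcome-defining measurements are controlled at baseline?**

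| Outcome component | Limited by eligibility | Matched | In the stated model |
|---|---|---|---|
| Fasting glucose | yes, 5.6–6.9 mmol/l | yes | not named |
| 2-h glucose | yes, up to 11.0 mmol/l | no | not named |
| HbA1c | yes, below 48 mmol/mol | no | not named |

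In Table 2 (intervention group only), 2-h glucose still spans 2.7–10.9 mmol/l with SD 1.6, and HbA1c 29–45 mmol/mol with SD 3.1. Eligibility leaves ample room for the groups to differ.

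**3. The planning effect, for scale.** Calculation of the sample size gives a control risk of 69/300 = 0.23 and a reduced effect of 6 points, so 0.23 − 0.06 = 0.17 in the intervention group. Under proportional hazards, HR = ln(1 − 0.17)/ln(1 − 0.23) = 0.71. The full effect (31/300) gives HR = ln(1 − 31/300)/ln(0.77) = 0.42.

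**4. Size of a possible bias.** The inputs are assumptions: a baseline difference of d SD in 2-h glucose, and a hazard ratio h per SD. With no true effect and the variable left out of the model, the spurious HR is about h^d, or 1/h^d if the intervention group starts lower.

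| d | Difference in mmol/l (d × 1.6) | h | h^d | 1/h^d |
|---|---|---|---|---|
| 0.2 | 0.32 | 1.5 | 1.08 | 0.92 |
| 0.3 | 0.48 | 1.5 | 1.13 | 0.89 |
| 0.2 | 0.32 | 2.0 | 1.15 | 0.87 |
| 0.3 | 0.48 | 2.0 | 1.23 | 0.81 |

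On the log scale, the ends of this range are 0.081/0.338 = 24% and 0.208/0.338 = 61% of the planned half-effect (ln 0.713 = −0.338). Against the full effect (ln 0.417 = −0.874) they are 9% and 24%.

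**5. A less approximate check.** Take a normally distributed covariate, a control risk of 0.23 and no true effect, and average the risk over the covariate in each arm. With h = 2.0, the apparent HR is 0.88 at d = 0.2 and 0.82 at d = 0.3, close to the simple formula. With a two-sided 5% two-proportion test and 267 per arm, the chance of a significant result is then about 11% and 18%. With h = 1.5 and d = 0.2 it is about 7%.

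**6. What would mimic the whole half-effect?** With h = 2.0, d = 0.338/ln 2 = 0.49 SD, or 0.49 × 1.6 = 0.78 mmol/l. That is larger than the differences illustrated above.

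**The case against.** The strongest reply is that the statistics section is three sentences in a condensed article. It calls study group a covariate; it does not say the only one, nor does it say unadjusted. A fuller analysis plan could add covariates. This stands as a limit on certainty. It does not remove the point, because the article does state its primary model, and that model as stated does not suit the design as described.

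Several stronger readings are tempting, and the documents do not support them:

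- **That the groups are in fact imbalanced.** Table 2 covers the intervention group only. Both the SD shift and the hazard ratio per SD are assumptions.
- **That 2-h glucose and HbA1c are wholly uncontrolled.** Eligibility caps both. Matching on fasting glucose, BMI, age and GRS removes part of any difference to the extent that these correlate with them. The relevant shift is what remains after matching, and it may be smaller than one expressed on the full SD of 1.6.
- **That volunteers are being compared with non-volunteers.** The article does not say how controls were approached. They come from the same cohort and attend visits at years 0 and 3, so they may be volunteers too.
- **That the comparison of effects between high and low GRS is equally exposed.** Participants and nutritionists were blinded to GRS, so self-selection is unlikely to depend on knowing it. A similar bias in both strata would largely cancel in that comparison. It would not cancel in the within-stratum hazard ratios, which are what the stated model estimates.
- **That the stated model wastes data or misdescribes the design.** The 635 intervention participants exceed the planned 600, but a Cox model that does not condition on matched sets keeps them all. The article also does not call this trial randomised.

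Individual matched sets are not documented either; the matching may have been at group level.

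**Conclusion.** The point holds in a limited form. The comparison between intervention and control is non-randomised. Two of the three glycaemic measurements that define the outcome are neither matched nor named in the primary model, so a residual baseline difference in either would bias the hazard ratio in each GRS group. The direction is unknown and the size cannot be fixed from the article. Under the assumed inputs it is about 0.81 to 0.92 or 1.08 to 1.23, that is, a quarter to three-fifths of the planned half-effect on the log scale. This is a vulnerability worth closing before outcomes are analysed, not evidence that the result will be wrong.

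**What to change.** In Statistical analyses, pre-specify the primary Cox model in each GRS group as study group plus:

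- baseline 2-h glucose and HbA1c, both continuous;
- the matching factors: fasting glucose, age, BMI and GRS.

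Show the unadjusted model as a supportive result. Add a sensitivity model with baseline physical activity, diet, smoking and alcohol. Use a robust variance by matched set only if the matching was individual, and state which kind of matching was done. Report the comparison as non-randomised.

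The cost is analysis wording only. The OGTT, HbA1c and questionnaires belong to the year-0 visit, which both groups attend. Fixing the covariates before the outcome data are examined also avoids choosing them after the fact.
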